### 3.3. Sample Size Estimation

For our primary objective, we estimated the required sample size based on previous TEM findings for kidney transplants [19]. To find a statistically significant difference in the proportion of patients with established endothelial damage (expected to be 0.29 in the non-exposed group and 0.71 in the exposed group) accepting an alpha risk of 0.05 and a beta risk of 0.2 in a two-sided test, 21 patients were deemed necessary for each group. 

For the secondary objectives, we obtained the estimation based on the previous data of intimal thickness assessments with IVUS: a change of intimal proliferation > 0.5 mm from the baseline to one year after HT was deemed a surrogate marker of allograft vasculopathy [18]. To find a statistically significant proportion difference (expected to be 0.27 in the non-exposed group and 0.6 in the exposed group) with an alpha risk of 0.05 and a beta risk of 0.2 in a two-sided test, we needed a two-sided test to enroll 35 patients for each group.

We expect that, in 10% of the exposed patients, we won’t be able to detect any tissue damage with the current diagnostic tools. Assuming a 10% dropout rate, we plan to recruit 45 patients per group between the 3 participant hospitals.

The recruitment of non-exposed patients may be hampered by difficulties in finding a coetaneous patient for every exposed patient. A contingency plan has been established with an agreement with three additional HT centers in Spain that would start recruiting patients in the case of difficulties in achieving the estimated sample size. 

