## 2. Introduction

Heart transplantation (HT) is the last therapeutic alternative for many patients with heart failure [1]. In recent years, the short-term survival for HT patients has markedly improved (85–90% survival rate in the first year after HT). However, the long-term survival has barely improved, remaining around 11 years [2]. Although there are many risk factors related to a late allograft dysfunction, the detection of anti-human leukocyte antigen (anti-HLA) antibodies is true for half of the patients [3,4] and the detection of donor-specific antibodies constitutes an independent predictor of a poorer survival in this population [5].

The management of patients with anti-HLA antibodies is not well-defined due to the lack of solid evidence, with no reliable data about “which antibodies are of clinical relevance, which patients to treat, and which treatments are most effective or safe” [6]. Thus, although the treatment of acute antibody-mediated rejection is well-established, there is a lack of evidence for managing chronic antibody-mediated injuries [7]. The current follow-up work-up of HT patients includes echocardiography, coronary angiography and an endomyocardial biopsy. The appearance of de novo anti-HLA antibodies with an otherwise normal work-up is relatively common. However, most of these patients finally develop a graft dysfunction. In this scenario, and for many patients, there are no appropriate treatments and re-transplantation is the only option. Nowadays, there is a trend towards a more aggressive approach to these patients to better understand the pathophysiology of the process. This often leads to the performance of the coronary angiography, right-heart catheterization and endomyocardial biopsy out of the established protocols.

This is why a detailed description of antibody-mediated chronic injuries is a necessary first step to lead us to develop evidence-based diagnostic and care protocols. 

An antibody-mediated injury is produced through the activation of the complement system, which leads to leukocyte migration, increased phagocytosis and a T cell-mediated immune response. The rapamycin pathway promotes cytoskeletal remodeling and immune cell proliferation and migration. This immune response finally leads to allograft vasculopathy and a late allograft failure. The time from the antibody detection to myocardial damage varies between patients from a few months to several years [8].

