○An assessment of the predictive performance of different diagnostic tools (CMR, transthoracic echocardiography, serum markers of fibrosis, intracoronary pressure guidewire and IVUS) to detect tissue damage using TEM, OM and IHC techniques as the combined reference standard. ○An estimation of the risk of adverse outcomes as a function of time from anti-HLA antibody positivity.

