### 3.4. Study Design

We designed a cross-sectional approach to address the primary objective of this project. 

All exposed and non-exposed participants will undergo a multimodal evaluation that consist of an endomyocardial biopsy and analyses with OM, TEM and IHC as well as transthoracic echocardiography and CMR, right-heart catheterization, coronarography, IVUS, a pressure guidewire assessment, an immunological study and the determination of the serum markers of fibrosis (Figure 2). 

The three participating hospitals are responsible for the patient recruitment and follow-up. The hemodynamic study tissue and blood sampling will be also performed at the recruiting center, according to an *ad hoc* protocol. The Spanish National Center for Cardiovascular Research acts as the imaging core lab, where every included patient is transferred for the imaging acquisition and further analysis. A multidisciplinary team consisting of pathologists, interventional cardiologists, cardiac imaging experts, immunologists and biologists of the host institution (University Hospital 12 de Octubre) will analyzed all performed tests (Figure 2). Those specialist responsible for the analysis are blind to the anti-HLA antibody exposure status of the participants. 

Figure 3 summarizes the timeline and the achieved milestones of this research project. 

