### 3.5. Assessment Variables

Primary outcomes: individual and combined structural graft injury outcomes based on the presence of microvascular inflammation, intimal or transmural arteritis or thrombotic microangiopathy (OM); linear C4d staining (%) (IHC); and endothelial edema and vacuolization (semi-quantitative score), subendothelial widening (pm) and basal membrane duplication (TEM). For the secondary objectives: ○Microvascular damage assessment: Index of microcirculatory resistance and coronary flow reserve (pressure guidewire), a CMR-based quantitative perfusion assessment (mL/min/100 g of tissue) and the capillary density (capillaries/mm^2^) (OM).○CMR T2 mapping (ms) to detect intracellular edemas (endothelial vacuolization).○CMR T1 mapping (ms) and CMR extracellular volume quantification (%) as well as TTE-based global longitudinal strain (%) to identify myocardial remodeling and fibrosis.○Fibroblast growth factor 23 (R.U./mL), procollagen type 1 carboxy-terminal propeptide (µg/L) and collagen type 1 C-terminal telopeptide (µg/L) as the serum markers of fibrosis and remodeling.○FFR (coronary physiology) and IVUS-based intimal thickness (mm) as early markers of coronary allograft vasculopathy. ○Rate of antibody-mediated rejection, anti-HLA antibody seroconversion, heart failure and death. 

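### Section 3.3 sizes the secondary objectives on a first-year IVUS change that the text gives no means of measuring, and that calculation powers neither stated secondary objective

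*Protocol article*

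**What the plan says.** All references are to the protocol article.

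- **Section 3.3** gives a separate calculation for the secondary objectives, taken from earlier IVUS data in which "a change of intimal proliferation > 0.5 mm from the baseline to one year after HT was deemed a surrogate marker of allograft vasculopathy". The proportions with that change are "expected to be 0.27 in the non-exposed group and 0.6 in the exposed group". The conclusion reads "with an alpha risk of 0.05 and a beta risk of 0.2 in a two-sided test, we needed" (after a repeated mention of the two-sided test) "to enroll 35 patients for each group". The section then mentions 10% of exposed patients without detectable damage and 10% dropout, and plans 45 per group. The primary objective has its own calculation: 0.29 versus 0.71, 21 per group.
- **Section 3.4**: "We designed a cross-sectional approach to address the primary objective of this project". IVUS is one component of the multimodal evaluation that every participant has. No repeat IVUS is described.
- **Section 3.5** lists, among the variables for the secondary objectives, "FFR (coronary physiology) and IVUS-based intimal thickness (mm) as early markers of coronary allograft vasculopathy".
- **Section 3.2** enters exposed patients when antibodies are detected, with a confirmatory test at least three months later. Comparators are chosen for a close transplant date. Neither rule fixes the time after transplantation at which the assessment falls.
- **Section 3.1** states two secondary objectives. One is the predictive performance of the diagnostic tools, IVUS included, against TEM, OM and IHC combined. The other is "An estimation of the risk of adverse outcomes as a function of time from anti-HLA antibody positivity".

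**The concern.** The endpoint in the calculation is binary and needs two IVUS measurements per patient, one at baseline and one a year after transplantation. The study as described takes one, at a time that varies between patients, and records a continuous thickness. Rates of 0.27 and 0.60 for growth over the first post-transplant year do not carry over, without justification, to a single thickness measured at differing times after transplantation.

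The contrast itself is also not a stated objective. Diagnostic performance depends on how many patients are positive and negative on the reference standard. Risk over time depends on the number of events. An exposed versus non-exposed difference in IVUS growth informs the precision of neither.

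At stake is the stated basis for enrolling 45 rather than about 26 per group in a study with invasive tests, together with an 80% power statement that readers would attach to the secondary results.

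**Working it through.** **1. Reproduce the plan's figure.** Inputs from section 3.3: p₀ = 0.27, p₁ = 0.60, two-sided α = 0.05 (z = 1.960), power 80% (z = 0.842), equal groups. With p̄ = (0.27 + 0.60)/2 = 0.435, the pooled-variance formula is

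n = [1.960·√(2·p̄·(1−p̄)) + 0.842·√(p₀(1−p₀) + p₁(1−p₁))]² / (p₁−p₀)²

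= [1.960·√(2·0.435·0.565) + 0.842·√(0.1971 + 0.2400)]² / 0.33²

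= (1.374 + 0.556)² / 0.1089 = 34.2, so **35 per group**. Power at 35 is 80.9%. The number stands.

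**2. Does it drive recruitment?** Section 3.3 does not show the step from 35 to 45. Applying both 10% allowances gives 35/0.9/0.9 = 43.2, so 44, close to 45. The same allowances on the primary calculation give 21/0.9/0.9 = 25.9, so 26. Only the IVUS calculation leads to the target.

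**3. Compare the calculation with the study described.**

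| Feature | Calculation (3.3) | Study as described |
|---|---|---|
| IVUS variable | change over 0.5 mm, yes/no | intimal thickness in mm (3.5) |
| Measurements per patient | two | one evaluation, no repeat described (3.4) |
| Timing | baseline and one year after transplantation | set by antibody detection and comparator selection (3.2) |
| Question | difference between exposure groups | diagnostic performance; risk by time from positivity (3.1) |

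**4. What 45 per group offers for the variable as listed.** With 10% dropout, 45 × 0.9 = 40.5, taken as 40 evaluable per group. For a two-sample t-test, two-sided 0.05, 80% power, the normal approximation gives d = (1.960 + 0.842)·√(2/40) = 0.626. The exact t calculation gives **0.63 SD**. The article gives no SD for thickness, so this cannot be put in mm.

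**5. What it offers for diagnostic performance.** The article gives no target sensitivity and no prevalence on the combined reference standard, so both are assumptions here. The half-width of a 95% interval is 1.96·√(s(1−s)/n₊). Take s = 0.80.
- n₊ = 40, from the TEM-based damage rates in 3.3 (40 × 0.29 + 40 × 0.71 = 40): 1.96·√(0.16/40) = 0.124, about ±12 points.
- n₊ = 60, if the combined standard classifies more patients as injured: 1.96·√(0.16/60) = 0.101, about ±10 points.

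**6. Clinical events.** The article gives no event rate or effect size, so nothing can be computed for the second objective.

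**7. Primary objective.** For 0.29 versus 0.71, the same pooled formula gives power of about 98% at 40 per group. It does not depend on the IVUS calculation.

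**The case against.** The strongest reply is that 3.3 borrows planning rates from a related published endpoint, which is common in a study that calls itself a pilot. IVUS intimal thickness is a listed secondary variable, IVUS is one of the tools in the first secondary objective, and greater thickness after long exposure is a stated hypothesis. This stands in part: the calculation is related to the study. It still does not power either objective, and section 3.3 does not present the rates as proxies.

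A reader might infer that no baseline IVUS exists and that the change can never be observed. The documents do not support that. The Introduction's statement, "The current follow-up work-up of HT patients includes echocardiography, coronary angiography and an endomyocardial biopsy", is general background and need not be exhaustive. The content of the local follow-up protocols is not given, and the workflow and timeline figures are not shown. Section 3.4 ties the cross-sectional approach to the primary objective, and the Abstract and section 3.6 mention longitudinal secondary outcomes. The follow-up-type outcomes listed are clinical (rejection, seroconversion, heart failure, death), and no serial IVUS is described. The supportable statement is that the text names no source.

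A reader might also infer that power falls once thickness is analysed as continuous. That is not shown. If 0.27 and 0.60 came from cutting a normal variable with equal spread in both groups, the implied difference would be 0.253 + 0.613 = 0.87 SD. At 40 per group a t-test would have about 97% power for that, against 86% for the binary comparison. If the rates do not transfer, the size and direction of any change in power are unknown.

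Finally, the ±12 points is not a figure of the plan. It rests on an assumed sensitivity of 0.80 and on damage rates for TEM alone.

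**Conclusion.** The point holds as wrong as written in section 3.3. The 35 per group is computed correctly, but for an endpoint and a contrast that the described design does not deliver, and the 45 per group appears to follow from it. The statement of 80% power for the secondary objectives is therefore unsupported.

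For thickness at one assessment, the study can detect about 0.63 SD with 80% power, assuming 40 evaluable per group and an unadjusted t-test. Precision for diagnostic performance is roughly ±10 to ±12 points on an assumed sensitivity of 0.80 with 60 to 40 reference-positive patients. No power figure can be given for clinical events. The conclusion is limited to the rationale for the secondary objectives: it does not show that 45 per group is too few, and it leaves the primary objective untouched.

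**What to change.** Keep 45 per group and reword section 3.3:

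1. Withdraw the statement that 35 per group gives 80% power for the secondary objectives.
2. For IVUS, name the variable as it will be measured: intimal thickness (mm) at the single assessment, compared between groups with adjustment for time from transplantation. State the detectable difference, about 0.63 SD at 40 evaluable per group. If earlier IVUS records supply the baseline and one-year values, say so instead, with their source.
3. For diagnostic performance, state the expected precision with its assumptions shown, for example about ±12 points at sensitivity 0.80 with 40 reference-positive patients and about ±10 points with 60.
4. Describe the clinical-event analysis as estimation only.

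The cost is a few sentences, with no extra patients or procedures. The article gives up a general power claim for the secondary objectives and gains figures that match what it will measure.

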### 3.4. Study Design

We designed a cross-sectional approach to address the primary objective of this project. 

All exposed and non-exposed participants will undergo a multimodal evaluation that consist of an endomyocardial biopsy and analyses with OM, TEM and IHC as well as transthoracic echocardiography and CMR, right-heart catheterization, coronarography, IVUS, a pressure guidewire assessment, an immunological study and the determination of the serum markers of fibrosis (Figure 2). 

The three participating hospitals are responsible for the patient recruitment and follow-up. The hemodynamic study tissue and blood sampling will be also performed at the recruiting center, according to an *ad hoc* protocol. The Spanish National Center for Cardiovascular Research acts as the imaging core lab, where every included patient is transferred for the imaging acquisition and further analysis. A multidisciplinary team consisting of pathologists, interventional cardiologists, cardiac imaging experts, immunologists and biologists of the host institution (University Hospital 12 de Octubre) will analyzed all performed tests (Figure 2). Those specialist responsible for the analysis are blind to the anti-HLA antibody exposure status of the participants. 

Figure 3 summarizes the timeline and the achieved milestones of this research project. 

### 3.5. Assessment Variables

Primary outcomes: individual and combined structural graft injury outcomes based on the presence of microvascular inflammation, intimal or transmural arteritis or thrombotic microangiopathy (OM); linear C4d staining (%) (IHC); and endothelial edema and vacuolization (semi-quantitative score), subendothelial widening (pm) and basal membrane duplication (TEM). For the secondary objectives: ○Microvascular damage assessment: Index of microcirculatory resistance and coronary flow reserve (pressure guidewire), a CMR-based quantitative perfusion assessment (mL/min/100 g of tissue) and the capillary density (capillaries/mm^2^) (OM).○CMR T2 mapping (ms) to detect intracellular edemas (endothelial vacuolization).○CMR T1 mapping (ms) and CMR extracellular volume quantification (%) as well as TTE-based global longitudinal strain (%) to identify myocardial remodeling and fibrosis.○Fibroblast growth factor 23 (R.U./mL), procollagen type 1 carboxy-terminal propeptide (µg/L) and collagen type 1 C-terminal telopeptide (µg/L) as the serum markers of fibrosis and remodeling.○FFR (coronary physiology) and IVUS-based intimal thickness (mm) as early markers of coronary allograft vasculopathy. ○Rate of antibody-mediated rejection, anti-HLA antibody seroconversion, heart failure and death. 

### 3.6. Data Collection and Statistical Analysis 

The study data are collected and managed using REDCap electronic data capture tools hosted at the Instituto de Investigación Sanitaria Hospital 12 de Octubre (imas12). REDCap (Research Electronic Data Capture) is a secure, web-based software platform designed to support data capture for research studies [20,21]. 

A clinical research coordinator (CRC) conducts the data management at the host institution. The CRC is responsible for reviewing the eCRFs and ensuring compliance with the registration protocol. Of the sample, 10% will be randomly selected for the data verification. 

The individual and combined primary outcomes of the structural graft injury and longitudinal secondary outcomes will be compared between the exposed and non-exposed groups with univariate and multivariable descriptive analyses. The predictive performance of CMR, TTE, coronary physiology parameters and IVUS will be assessed with univariate and multivariable modelling. A parsimonious approach will be implemented to propose a standard assessment protocol, including a predictive score based on the study results. All statistical analyses will be obtained using dedicated software (StataCorp. 2021. Stata Statistical Software: Release 17. StataCorp LLC., College Station, TX, USA).

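### The predictive score meant to support a standard assessment protocol rests on about 40 injured patients and 9 to 12 candidate measures, and its analysis sentence omits the serum markers

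*Protocol article*

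**What the plan says.** The first secondary objective (section 3.1) is to assess how well several tools, namely "CMR, transthoracic echocardiography, serum markers of fibrosis, intracoronary pressure guidewire and IVUS", perform "to detect tissue damage using TEM, OM and IHC techniques as the combined reference standard".

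Section 3.6 gives the analysis: "The predictive performance of CMR, TTE, coronary physiology parameters and IVUS will be assessed with univariate and multivariable modelling". It then names the product: "A parsimonious approach will be implemented to propose a standard assessment protocol, including a predictive score based on the study results".

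Section 3.5 lists the measures for the secondary objectives. Leaving out capillary density, which is itself a histological reading, there are 12: index of microcirculatory resistance, coronary flow reserve, CMR perfusion, T2, T1, extracellular volume, global longitudinal strain, three serum markers, fractional flow reserve and IVUS intimal thickness.

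Section 3.3 derives 21 per group from endothelial damage rates of 0.29 and 0.71, and 35 per group from intimal proliferation rates of 0.27 and 0.60. It then allows for dropout ("Assuming a 10% dropout rate") and concludes: "we plan to recruit 45 patients per group between the 3 participant hospitals". It gives no sample size for the score.

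**The concern.** The sample size and the intended use of the score do not match. A study sized to detect two large differences between groups is also asked to yield a multivariable score that supports a standard protocol. With few outcomes per candidate, a fitted model follows chance features of its own sample. Its accuracy there is then too good and its predicted risks are too extreme for new patients. Choosing a smaller model from the same data does not remove this, because the choice is itself driven by chance. A protocol proposed on such figures could favour the wrong tests, some of them invasive, and promise accuracy that later patients would not show.

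A second, simpler problem is that the objective lists five kinds of tool and the analysis sentence covers four. Serum markers of fibrosis are missing from it.

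**Working it through.** **1. The plan's own sample sizes.** Two-sided alpha 0.05, power 0.80, pooled normal formula:

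n = [1.960·√(2·p̄·(1−p̄)) + 0.842·√(p1(1−p1) + p2(1−p2))]² / (p1−p2)²

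- 0.29 v 0.71: (1.386 + 0.540)² / 0.1764 = 21.03, so 22 if rounded up. The arcsine form gives 20.9, so the stated 21 is reproduced to within rounding.
- 0.27 v 0.60: (1.374 + 0.556)² / 0.1089 = 34.2, so 35, as stated.
- Applying both 10% allowances in section 3.3: 35/0.9/0.9 = 43.2, so 44, close to the 45 planned.

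The group comparisons are therefore adequately sized. None of these figures concerns the score.

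**2. Outcomes available for the score.**

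- Evaluable: 2 × 45 × 0.9 = 81.
- Injured: 40.5 × 0.29 + 40.5 × 0.71 = 40.5.
- Per candidate: 40.5/12 = 3.4 with all measures; 40.5/9 = 4.5 without the serum markers.

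The 0.29 and 0.71 rates are for endothelial damage and come from kidney-transplant TEM. Using them for the combined TEM/OM/IHC reference is an assumption. It is also the favourable case: among 81 patients, the smaller of the injured and uninjured groups cannot exceed 40. If the reference were positive in 30% or 70% (illustrative), the smaller group would be 81 × 0.30 = 24.3, or 2.0 per candidate with 12 and 2.7 with nine.

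**3. Patients needed to develop a score.** Two standard criteria were used, and the larger result taken: expected shrinkage of at least 0.90, and optimism in Nagelkerke R² of at most 0.05. The first is n = P / [(0.9−1)·ln(1 − R²/0.9)], with P candidates and R² the Cox-Snell value implied by an assumed AUC at a 50% outcome share. Example: AUC 0.80 gives R² = 0.261, so ln(1 − 0.29) = −0.3425 and n = 12/0.03425 = 350.

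| Candidates | AUC 0.70 | AUC 0.75 | AUC 0.80 | AUC 0.85 |
|---|---|---|---|---|
| 12 | 829 | 520 | 350 | 254 |
| 9 | 622 | 390 | 263 | 191 |
| 3 | 208 | 130 | 88 | 64 |
| 2 | 139 | 87 | 59 | 43 |

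Against 81 available, neither 9 nor 12 candidates comes close at any of these AUCs. Two or three prespecified predictors are near the range or inside it if the true AUC is about 0.80 or more.

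**4. Size of the optimism if performance went uncorrected.** Logistic models were simulated at n = 81 with 300 runs per setting, three true predictors, correlation 0.3 and a 50% outcome share. Results for a true AUC of 0.75:

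| Candidates | Model | Apparent AUC | AUC in new patients | Calibration slope |
|---|---|---|---|---|
| 12 | full | 0.827 | 0.687 | 0.42 |
| 12 | backward, p 0.10 | 0.787 | 0.665 | 0.46 |
| 12 | backward, p 0.05 | 0.758 | 0.650 | 0.49 |
| 9 | full | 0.810 | 0.701 | 0.52 |
| 9 | backward, p 0.10 | 0.772 | 0.670 | 0.53 |
| 9 | backward, p 0.05 | 0.752 | 0.656 | 0.54 |

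Over true AUCs of 0.70 to 0.80, the overstatement is 0.10 to 0.16 with 12 candidates (slope 0.33 to 0.53) and 0.09 to 0.13 with nine (slope 0.43 to 0.59). Backward selection narrows the gap slightly but gives a lower AUC in new patients than the full model. With no true signal, 12 candidates still show an apparent AUC of 0.58 to 0.72.

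**5. Serum markers.** Section 3.1 names them among the tools to be assessed. Section 3.4 has them measured in all participants, and section 3.5 lists the three assays. The modelling sentence in section 3.6 names CMR, echocardiography, coronary physiology and IVUS only.

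**The case against.** The strongest reply is that the article is a condensed account. Internal validation, shrinkage and calibration are usually left to an analysis plan, and this one may contain them. That stands. A reader might infer that the score will be judged on the same patients used to build it, or that univariate screening will feed the multivariable model. The text says neither. Univariate and multivariable modelling can equally mean each test alone and then the tests together. The overstatement above is therefore conditional on uncorrected reporting.

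The article also calls the study a pilot that prepares later dedicated studies, and the score is only to be proposed. This softens the stakes. However, section 3.6 does not carry the exploratory label over to the score. An analysis plan could correct the reported accuracy, but it could not make about 40 injured patients enough to choose reliably among 9 to 12 measures. Both the sample size and the use of the score are fixed in this document.

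A reader might also infer that recruiting exposed and non-exposed patients 1:1 miscalibrates predicted risks. The documents do not support this. The introduction puts anti-HLA detection at about half of patients, and at that share the ratio alone causes no shift. Prevalence under the study's stricter definition (intensity thresholds plus a confirmatory test) may differ, but no figure is given.

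On the serum markers, it would go too far to say they will not be evaluated. They are measured and listed, and the gap may be one of wording.

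**Conclusion.** The point holds in a limited form. The study is adequately sized for its group comparisons but not for a score drawn from 9 to 12 candidates, at 3.4 to 4.5 injured patients per candidate. If performance were reported without correction, the AUC would be too high by roughly 0.09 to 0.16 and the calibration slope in new patients would be about 0.33 to 0.59. These sizes rest on assumptions: the 0.29 and 0.71 rates standing in for the combined reference, true AUCs of 0.70 to 0.80, three true predictors and correlation 0.3. The shortfall itself does not depend on the rates, since no other injury share would enlarge the smaller outcome group.

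The omission of serum markers from the analysis sentence needs no assumption and should be reconciled with the objective. No conclusion is drawn about miscalibration from the 1:1 ratio, nor that validation is absent from the full plan.

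**What to change.** - Add the serum markers of fibrosis to the modelling sentence in section 3.6, so that it matches the secondary objective.
- Fit either a penalised logistic model on prespecified candidates or a model limited to two or three predictors named in advance.
- Report bootstrap optimism-corrected AUC and calibration slope, repeating any selection step within each resample.
- Call the score exploratory and require external validation before it supports a standard protocol, in line with the study's stated pilot aim.

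This needs no extra patients or tests. It costs a little more analysis, and the reported accuracy will be lower than the uncorrected figures. If two or three predictors are prespecified, the remaining measures can still be described one at a time.
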